#### 2.5.3 Data collection

##### 2.5.3.1 Primary outcomes

###### 2.5.3.1.1 Assessment of the trunk and hamstring muscle fatigue

Electromyography signals from the hamstring and trunk muscles will be recorded using the Delsys Trigno™ wireless EMG system. These muscles will be the erector spinae muscles at level L1 (Elfving et al., 2002a), the lumbar multifidus at the L5 level (Larivière et al., 2003), and medial hamstring muscles (Fiebert et al., 1997). These measurements will be taken at baseline, post-fatigue protocol, and post-recovery modalities (immediately and after 15 min). Following skin abrasion and cleansing with alcohol, electrode pairs will be placed bilaterally on the targeted muscles (Elfving et al., 2002b). The inter-electrode distance will be 2.5 cm (Areeudomwong et al., 2012a) on erector spinae muscles and the lumbar multifidus. The electrode for the medial hamstring will be positioned midway between the ischial tuberosity and the medial epicondyle of the tibia. During the tests for maximum isometric strength of the back extensor and hamstring muscles, sEMG recordings will respectively be collected from the multifidus and longissimus muscles (erector spinae), as well as from the medial hamstring muscles. Each sEMG measurement episode will have a standardized duration of 5 s, during which continuous recording occurs. The raw sEMG signals will be recorded with a sampling frequency of 2000 Hz and the bandwidth of sEMG will be around 20Hz–450 Hz (Larivière et al., 2003). The characteristics of muscle fatigue detected by EMG include a shift from a high-frequency spectrum to a low-frequency spectrum and an increase in amplitude (Sakurai et al., 2010). The assumption is that recovery and fatigue are mutually exclusive. Therefore, the shift from a low-frequency spectrum to a high-frequency spectrum and a decrease in amplitude are indicative features of muscle recovery detected by EMG. In this study, the absolute values of the frequency features (median frequency MDF, and mean power frequency, MPF) and the mean amplitude (root mean square, RMS) of the sEMG signals during the middle 3 s of the 5-s testing period will be employed to assess muscle fatigue and recovery. To ascertain these variables, the raw EMG signal will undergo processing using a fast Fourier transformation.

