## 1 Introduction

The modern lifestyle has led human societies toward a more sedentary existence (Stockwell et al., 2021; Chaudhary et al., 2024). The literature indicates that, in the future, three-fourths of all jobs worldwide will be sedentary (Khanzadeh et al., 2020). Sedentary behavior is described as “any waking activity with an energy expenditure of 1.5 METs or less while sitting, reclining, or lying down.” (Lassalle et al., 2021). Given that desk workers spend a considerable portion of their time seated, they could be potential targets for interventions aimed at reducing sedentary behavior (Barone Gibbs et al., 2018). This type of lifestyle is associated with musculoskeletal disorders, particularly when sitting is prolonged in uninterrupted bouts (Chia et al., 2015).

Prolonged sitting with ongoing contraction of the trunk muscles can lead to fatigue in the deep trunk muscles (Waongenngarm et al., 2016; Waongenngarm et al., 2018; Saiklang et al., 2022a; Saiklang et al., 2022b), which, in turn, can alter the neuromuscular system and result in core stability disorders (Jabłońska et al., 2021). This is because the neuromuscular system is responsible for creating the conditions necessary for adequate core stability through the coordinated contraction of the trunk muscles (Esmaeili and Askari, 2020).

Also, muscle fatigue can affect postural stability. Under fatigue, afferent feedback is disrupted, impairing joint proprioception and subsequently affecting somatosensory input (Tajali et al., 2022). Reduced efficiency in muscle contraction (Tajali et al., 2022), inadequate processing of sensory input, and compromised neuromuscular performance due to fatigue can disrupt both feedforward and feedback control of postural sway (Zemková et al., 2021a). Typically, a decline in postural stability is observed with muscular fatigue (Akulwar and Mulgaonkar, 2017). Especially, strategies of postural control can alter under muscle fatigue (Johanson et al., 2011). For instance, a study by Johanson et al. showed that the strategies used by fatigued individuals, when faced with increased postural demands, are similar to those utilized by individuals experiencing recurring low back pain. Fatigued healthy individuals exposed to a sudden perturbation have demonstrated an elevation in electromyographic amplitude, longer activation latencies, diminished muscle activity, and heightened co-contraction (Zemková et al., 2021a; Zemková et al., 2021b).

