Given the fact that impaired core and postural stability strongly correlates with hamstring and trunk muscle corset conditions, it becomes crucial to restore optimal muscle capacity and efficiency. Physical exercises offer a potentially feasible option to reduce sedentariness at work without major disruption to office work practices. During core exercises, fatigued trunk muscles show an increase in EMG root mean square amplitude values. Specifically, two studies demonstrated that the abdominal drawing-in maneuver (Saiklang et al., 2021), as well as a combination of the abdominal drawing-in maneuver with supported dynamic lumbar extension (Saiklang et al., 2022a), increased the activation of the transversus abdominis (TrA) and internal oblique (IO) muscles. Additionally, the abdominal drawing-in technique led to higher activation ratios of TrA and IO compared to the rectus abdominis, highlighting its effectiveness in engaging these key muscles for spinal support. In another study, Abdelraouf and Abdel-Aziem demonstrated that core stability interventions can alter the recruitment patterns of core muscles (Abdelraouf and Abdel-Aziem, 2016), and effectively improve the fatigue resistance of these muscles, thereby restoring core stability (Zou et al., 2021). Trunk stabilization exercises aim to enhance and regain the coordinated contraction of both local and global muscles, improving control over the pelvis and lumbar spine (Richardson et al., 1999; Hodges, 2003). This also helps the trunk muscles regain their ability to fulfill the requirements of postural control (D’souza et al., 2022). Training with trunk stabilization exercises has shown significant improvements in core stability (Butcher et al., 2007; Sato and Mokha, 2009), and immediate improvements in static and dynamic balance (Kaji et al., 2010; Imai et al., 2011; Imai et al., 2014a; D’souza et al., 2022). Also, Szafraniec et al. demonstrated improvement in the mediolateral body balance after core exercise (Szafraniec et al., 2018). These effects were noticeable within a span of 30 min post-exercise and persisted for a minimum of 24 h. An enhanced automatic response in maintaining a stable upright posture was observed 24 h after the exercise session. However, there has been little discussion so far about the efficiency of trunk stability exercise in the recovery of core and postural stability during prolonged sitting at the workplace.

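### A fall in EMG amplitude is fixed as a sign of recovery, but amplitude is recorded in maximal contractions, where its direction under fatigue is not determined

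*Protocol article*

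**What the plan says.** All of the following is in the protocol article, section 2.5.3.1.1, the first entry under Primary outcomes.

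- **Task.** The recording task is maximal: "During the tests for maximum isometric strength of the back extensor and hamstring muscles, sEMG recordings will respectively be collected". No other contraction is described for the EMG measurements.
- **Measure.** The analysis uses "the absolute values of the frequency features (median frequency MDF, and mean power frequency, MPF) and the mean amplitude (root mean square, RMS") over the middle 3 s of a 5-s effort. No scaling to force or to a reference contraction is stated.
- **Direction under fatigue.** Fatigue is said to show as "a shift from a high-frequency spectrum to a low-frequency spectrum and an increase in amplitude".
- **Direction under recovery.** This is the mirror image: "Therefore, the shift from a low-frequency spectrum to a high-frequency spectrum and a decrease in amplitude are indicative features of muscle recovery detected by EMG". The ground given is "The assumption is that recovery and fatigue are mutually exclusive".
- **Timing.** The measurements are made at baseline (T1), after the fatigue protocol (T2), immediately after the recovery modality (T3) and 15 min later (T4).

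The Introduction (section 1) supports an amplitude rise in a different task: "During core exercises, fatigued trunk muscles show an increase in EMG root mean square amplitude values".

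**The concern.** An amplitude rise with fatigue is what one expects when a tired muscle must still meet a set demand: more activation is needed for the same output. A maximal strength test sets no such demand. The participant gives what they can, and RMS reflects the drive reaching the muscle as well as any effect of fatigue on the signal. These two influences can pull in opposite directions, so the net sign is open. This premise is general measurement knowledge; the protocol neither states nor contradicts it.

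The T2 test follows at least four rounds of eight trunk exercises, continued until a Borg score of 17 (section 2.5.4). A lower maximal drive at T2 is therefore foreseeable. If it occurs and is large enough, RMS falls with fatigue and rises as the muscle recovers. A modality that restores drive could then be described, on RMS, as leaving the muscle more fatigued than one that restores nothing. RMS and the frequency measures could also point to opposite conclusions about the same modality.

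**Working it through.** The protocol gives no figure for this point, so there is none to reproduce. The check is of sign.

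**Inputs**
- From section 2.5.3.1.1: maximal test, absolute RMS, a rise means fatigue, a fall means recovery.
- Assumed, because the document gives neither: *g*, the factor by which fatigue raises amplitude at equal drive, from 1.0 to 1.3; and *d*, the proportional loss of drive at T2, from 0 to 40%.

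**Formula**

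RMS at T2 / RMS at T1 = *g* × (1 − *d*)

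The protocol's direction is right only if this exceeds 1, that is, if *d* < 1 − 1/*g*.

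**Results: change in RMS from T1 to T2**

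| *g* | break-even *d* | *d* = 0 | 10% | 20% | 30% | 40% |
|---|---|---|---|---|---|---|
| 1.0 | 0% | 0% | −10% | −20% | −30% | −40% |
| 1.1 | 9.1% | +10% | −1% | −12% | −23% | −34% |
| 1.2 | 16.7% | +20% | +8% | −4% | −16% | −28% |
| 1.3 | 23.1% | +30% | +17% | +4% | −9% | −22% |

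**Two cases followed through to full recovery (RMS back at its T1 value)**
- *g* = 1.1, *d* = 20%: the T2 ratio is 1.1 × 0.8 = 0.88, a 12% fall, which has the direction assigned to recovery. Return to baseline is 1/0.88 = 1.136, a 13.6% rise, which has the direction assigned to fatigue. A modality that changes nothing stays at 0.88 and looks better on RMS than one that restores the muscle fully.
- *g* = 1.3, *d* = 10%: the T2 ratio is 1.3 × 0.9 = 1.17, a 17% rise. Return to baseline is 1/1.17 = 0.855, a 14.5% fall. Here the stated rule gives the right sign both times.

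**Share of the EMG outcome.** Three muscles × 2 sides × 3 indices = 18 EMG variables per assessment, of which 3 × 2 = 6 are RMS. This count leaves out the centre-of-pressure and centre-of-mass variables, which are also primary.

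**Support within the document.** The Introduction's statement on RMS concerns core exercises, not maximal tests. Its other relevant sentence lists "an elevation in electromyographic amplitude, longer activation latencies, diminished muscle activity, and heightened co-contraction" in fatigued people, but these are responses to a sudden perturbation, so it does not settle the direction in a maximal test either way.

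**The case against.** The strongest reply has five parts.

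1. *The premise is not in the document.* The protocol cites a source for the amplitude rise, and the task used there cannot be seen. This stands as a limit: it cannot be shown from the document that the rule is false, only that nothing in the document makes it hold for a maximal test.
2. *The reversal is conditional.* This stands. A reader might infer that the rule is always backwards in maximal contractions. The table does not support that: with enough amplitude gain and little loss of drive, the stated direction is correct.
3. *The features are described jointly.* Recovery is an upward spectral shift and a fall in amplitude together, so a fall in RMS alone does not match the pattern, and T2 is labelled post-fatigue by design, with Borg scores to confirm it. This makes a gross misreading at T2 less likely. It does not help at T3 and T4, where the question is how far each modality has recovered the muscle and RMS contributes with a preset sign.
4. *The analysis does not use the rule.* Section 2.7 tests modality, time and their interaction without a directional test. This stands: RMS estimates and p-values are unchanged, and only what is concluded from them is at risk.
5. *Detail may sit elsewhere.* Scaling to force, or a rule for discordant indices, may be in a fuller document. Their absence from the article is not held against it. The point is the direction that the article does state.

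**Conclusion.** The point holds in a limited form. The protocol assigns a recovery direction to absolute RMS in a task that does not determine that direction. The assignment rests on treating recovery as the mirror of fatigue, and nothing in the document fixes the force level or scales RMS in a way that would secure the sign. Under the assumed amplitude gains of 1.0 to 1.3, a loss of drive above 0% to 23% is enough to reverse it. The documents do not say whether losses of that size will occur.

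The reach is one of three primary EMG indices. The directions of median and mean power frequency are not in question. A reader might infer that the comparison of the modalities as a whole is undermined. The document does not support that: the stated purpose is recovery of core and postural stability, and the centre-of-pressure and centre-of-mass outcomes do not depend on this rule. The issue is moderate and concerns interpretation.

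**What to change.** In section 2.5.3.1.1, for the maximal tests:

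- Delete the fall in amplitude as a sign of recovery and the rise in amplitude as a sign of fatigue.
- State that EMG fatigue and recovery are judged on median frequency and mean power frequency.
- Report RMS descriptively at T1 to T4 with no preset recovery direction. Present it beside the force from the same strength test if that force is recorded. The section names an EMG system but no force-measuring device, so the availability of force should not be taken for granted.

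This should be done before the EMG data are examined, since a direction chosen afterwards would be post hoc.

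The cost is a change of wording; both frequency measures are already planned. The downside is that RMS no longer counts as a directional recovery endpoint. Keeping a direction for amplitude would require a contraction held at a fixed sub-maximal force. The protocol does not contain one, and adding it would be a change of procedure, not of wording.

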###### 2.5.3.1.2 Assessment of the postural and core stability

The participants will stand on a force plate without shoes, with their arms naturally hanging by their sides. They will be asked to maintain an upright position with one foot directly in front of and touching the other foot. Participants will self-select the forward foot. Postural stability measurements will be taken at baseline, post-fatigue protocol, and post-recovery modalities (immediately and after 15 min).

Trials will be conducted under a variety of conditions in a randomized order: (1) Tandem stance on a force plate with eyes open, (2) Tandem stance on a force plate with eyes closed, (3) Tandem stance on a foam mat (Airex Balance Pad) positioned on the force plate with eyes open, (4) Tandem stance on a foam mat (Airex Balance Pad) situated on the force plate with eyes closed (Zemková et al., 2016). Each participant will complete one set lasting 30 s under each condition. There will be a short break between every two trials (Zemková et al., 2021a).

####### 2.5.3.1.2.1 Measurement of center of pressure (CoP) variables under stable and unstable conditions

The FiTRO Sway Check (FiTRONiC, Bratislava, Slovakia) will be utilized for conducting an assessment of postural stability. The system detects the real force at the corners of the force plate and computes the instantaneous CoP position. It operates at a sampling rate of 100 Hz, with a 12-bit analog-to-digital signal conversion. The resolution of the CoP position is finer than 0.1mm, and it can measure within a range of 0–1,000 units per second. Non-linearity is within ±0.02% of the full scale, with a combined error of 0.03%. Sensitivity is at 2 mV/V±0.25%, and each sensor has an overload capacity of up to 150% of its range. Repeated measurements showed that reliability of CoP variables is consistently high, ranging from good to excellent, with no noteworthy fluctuations observed across consecutive days. The Romberg quotient, which involves calculating the sway ratio with eyes closed *versus* eyes open (EC/EO), will also be computed. Postural stability variables will be recorded using the FiTRO Sway Check (FiTRONiC, Bratislava, Slovakia) during unstable conditions. The apparatus comprises a square platform upheld by four springs possessing an elasticity coefficient of 40N/mm. When the center of pressure is shifted horizontally, the body weight distribution changes at the four corners of the platform. The force at each corner is determined by multiplying the spring’s elasticity coefficient by the vertical distance measured using a precise sensor. Analog signals are converted to digital (AD-converted) and sampled by computers at a rate of 100 Hz. Calculations of the instantaneous CoP position relies on the distribution of force across the four corners of the platform. Basic parameters of postural stability (i.e., mean CoP displacements in medio-lateral and anterior-posterior directions and mean CoP velocity) will be analyzed (Zemková et al., 2021b).

####### 2.5.3.1.2.2 Measurement of center of mass (CoM) variables under stable and unstable conditions

Concurrently, the Gyko inertial sensor system (Microgate, Bolzano, Italy) will be employed to evaluate center of mass (CoM) variables. These sensors will be fastened with an elastic belt on the participant’s posterior trunk, close to the body’s center of mass. The height of the Gyko device positioned on the trunk will be adjusted prior to measurement to mitigate any potential influence on the collected data. The Gyko system comprises a 3D accelerometer for measuring linear accelerations experienced by the device, a 3D gyroscope for measuring the device’s angular velocities, and a 3D magnetometer for measuring the magnetic field surrounding the device. It provides data measurements at a frequency of up to 1,000 times per second (1 kHz), ensuring a high temporal resolution of the collected data. Using these data as a foundation, specialized software algorithms are employed to delineate the kinematics of the analyzed body segment. It calculates three primary measures of body sway: sway travel speed, sway length and area, and sway frequency (Zemková et al., 2021a).

##### 2.5.3.2 Secondary outcomes

###### 2.5.3.2.1 Assessment of the back and hamstring muscles’ flexibility

The flexibility of right and left trunk side flexion and rotation, and also a range of movement hip flexion will be measured using the Gyko inertial sensor system (Microgate, Bolzano, Italy). This device can supply acceleration (up to 16 g), angular velocity (up to 2000°/s), and magnetic field measurements via a built-in 3D accelerometer, a 3D gyroscope, and a 3D magnetometer, respectively, with an acquisition frequency of 1,000 Hz. Using Bluetooth 4.0, data will be streamed to a computer with dedicated software (Gyko Repower; Microgate, Bolzano, Italy). It will be possible to display and store it for future use and analysis using computer software (Fonta et al., 2021). A good reliability and excellent concurrent validity of this device have been revealed (Hamersma et al., 2020).

####### 2.5.3.2.1.1 Measurement of back muscles flexibility

The device will be attached to a vest, which will be worn and adjusted on each subject’s upper torso during testing. So, the sensor will be located between the two scapulae at the level of the roots of the scapulae spines. The active range of trunk side flexion will be measured with each subject in the upright standing position while facing and maintaining the palmar surface of their hands in contact with the wall. Each subject will be advised to flex their trunk to the right and left sides by sliding their hands on the wall, avoiding forward bending or twisting of the trunk. They will keep their elbows and knees straight, as well as their heels on the ground. The active range of trunk rotation will be measured in the horizontal level with each participant in the upright sitting position. The effects of the potential lower body and pelvic movements on trunk rotation measurements will be prevented by instructing each subject to gently pressure a cylindrical cushion that will be placed between their knees (Fonta et al., 2021).

####### 2.5.3.2.1.2 Measurement of hamstring muscle flexibility

To measuring the range of movement hip flexion a standard procedure for the passive straight leg raise test will be adopted. Subjects will be first instructed to lie supine on a medical bed. The Gyko will be strapped at the level of the distal end of the femur of the tested leg. Inelastic straps will be used to fix the contralateral limb to the medical bed. The tested leg will be then passively lifted in full extension to the limit of the available range of motion, or the point the subjects started to feel pain or discomfort. The procedure will be repeated for both limbs. The testing order of the limbs will be randomized across subjects (Thomas et al., 2022).

Flexibility measurements will be performed at baseline, post-fatigue, and following the recovery modality (immediately and after 15 min).

#### 2.5.4 Fatigue protocol

Fatigue in the trunk muscles will be induced using the modified Abt protocol (Abt et al., 2007). This protocol consists of four sequential cycles, each containing eight exercises, with the entirety of the protocol lasting 32 min. The exercises within each set are organized in the following order: 1) seated trunk rotation using a medicine ball, 2) static torso extension while prone with a medicine ball, 3) supine lower torso rotation with a medicine ball, 4) inclined bench sit-ups with a weight plate, 5) side binding with a weight plate, 6) lumbar extension rotation with a weighted plate, 7) standing trunk rotation with pulley resistance, and 8) holding a supine isometric bridge position. Weight plates will be chosen for each subject on a different day prior to testing. Subjects will use the heaviest weight that allows them to perform each exercise 20 times within 40 s while maintaining proper form. Before initiating the fatigue protocol, a 10-min warm-up will be conducted, comprising 5 min of *in situ* warming followed by 5 min of aerobic stretching, with a focus on the trunk and hamstring muscles. Following the warm-up, the fatigue protocol will commence, during which participants will complete 20 repetitions of each exercise within a 40-s timeframe. There will be a 20-s pause between each exercise. The protocol will end under two conditions: firstly, when participants can no longer maintain correct form during the final set of exercises, and secondly, when they are unable to complete each repetition within a 2-s timeframe during the last set. After each phase of the protocol, the Borg scale will be utilized to evaluate participants’ perceived exertion, ranging from 6 to 20, to monitor fatigue levels (Borg, 1970). A score of six signifies no fatigue. If participants report a score of 17 or higher on the Borg scale at the end of the fourth round, the protocol will end. If they report a lower score, they should continue with another round until they reach a score of 17 (Askari and Esmaeili, 2021).

